## 12.3 Adverse event log

Adverse events caused by intervention, observations suspected to have a causal relationship with intervention, adverse events reported by subjects (whether or not serious) and abnormal detection parameters should be recorded in the case report form. A diagnostic rather than a symptom should be recorded. All adverse events will be recorded in detail with the purpose of 1) providing sufficient information to judge adverse events (such as whether the event should be classified as serious adverse events); 2) assessing the causality of adverse events between the intervention and trial. Each adverse event (or its sequelae) or abnormal detection parameters will always be followed up to its cure, alleviate or stabilize at an investigator acceptable level.

## 12.4 Causality and severity assessment

Principal investigator will promptly review records of adverse events and abnormal detection parameters to determine 1) whether the abnormal detection parameters should be classified as an adverse event; 2) whether there are evidences to prove adverse events associated with the study intervention; 3) whether it is serious adverse event. Each adverse event is logged as "probably relevant" or "may not be relevant." If the causality is ambiguous, it is considered as "probably relevant".

The degree of each adverse event should be evaluated and recorded as one of the following:

- Mild: Subjects with symptoms or signs may inform investigator. Subjects had symptoms or signs but easily tolerated.
- Moderate: Symptoms affect the normal activities and treatment may be required.
- Severe: Patients always feel these symptoms influencing their daily lives and medical interventions are needed.

## 12.5 Immediate action following a serious adverse events

During the period of informed consent form signed to all subjects completing the trial (the end of last follow-up), if any serious adverse events occurred, investigators should fill "serious adverse event reporting form" immediately, call and send fax or e-mail to relevant safety monitor person within 24 hours. Contacts as follows:

[contact]

[contact]

E-mail: [contact]

Unless the subjects were lost to follow up, investigators should monitor and follow up all serious adverse events found in the study to symptoms stabilize or final results of adverse events clarity. Meanwhile, investigator should provide the necessary treatment and follow-up. Any new events (or follow-up information) occurred in the previous reported serious adverse events, its reporting methods and deadlines are the same as initial report.

Investigators should report adverse reactions to the Shanghai Adverse Drug Reaction Monitoring Center according to the requirements of *Management measures on adverse drug reaction reporting and monitoring*.

# 13 Ethics

The study has been approved by Ethics Committee of Renji Hospital Shanghai Jiaotong University School of Medicine (Reviewed by Ethics Committee of Renji, No.[2010] 067).

**Primary Screening Test Form (Page 2 to 5)**

| **Patient Name：** | **Medical record number #：** |
| --- | --- |
| **Study No.：** | **Time of Signing the Letter of Consent：YTD** |
| **Date of Birth：YTD** | **Age：Year** |
| **Tel 1：**  **Level of Education：** | **Tel 2：** |

**Medical History**

1. Do you have a previous history of any one of the following diseases or discomforts?

1a. any one of the following diseases or conditions □ No

□ Yes

Whether or not take medicines for current treatment？□Yes □No

(Please record your therapeutic medication: ____________________)

Is the disease control satisfactory？□Yes □No

1b. Thyroid disease□ No

□ Yes

Whether or not take medicines for current treatment？□Yes □No

(Please record your therapeutic medication: ____________________)

Is the disease control satisfactory？□Yes □No

1c. Diabetes (unrelated to pregnancy) □No

□Yes

Whether or not take medicines for current treatment？□Yes □No

(Please record your therapeutic medication: ____________________)

Is the disease control satisfactory？□Yes □No

1d. Diagnosed with symptoms of heart disease □No

□Yes

After medical consultation , is your heart function able to withstand pregnancy？□Yes □No

1e. History of deep vein thrombosis □No □Yes

1f. Confirmed / suspected malignancy at cervical, breast or endometrial and other parts？□No □Yes

1g. Have you suffered from tuberculosis over the past six months？□No □Yes

2. Are you taking the following medications or receiving treatments as follows?

□Chinese medicinal herb / Chinese patent drug

□Multi-vitamin/folic acid

□Acupuncture and moxibustion

□None of the above

**Menstrual history**

1. Your age of menarche？ __ __year old

2. How many days between two menstruation start dates？The longest period： __days；The shortest period：__days

3. Have you used gynecological drugs to regulate the menstrual cycle?

□Yes □No

What kind of gynecological drugs have you ever used to regulate the menstrual cycle?

□Oral contraceptive pill

□Progesterone

□Traditional Chinese medicine

□Artificial cycle

4. Date of last menstrual period：//（Year / Month / Day）

**History of infertility**

1. How long is your pregnancy test？__ years
2. What is the cause of infertility diagnosed by your attending physician?

2a. Your diagnosis？（Please check all that apply）

□Ovulation failure

□Tubal factor

□Male factor

□Other factors or unknown causes

3. Have you received progesterone treatment？□No（if no, jump to the gynecological history）

□Yes

□Insulin Sensitizer（Metformin, rosiglitazone, or others）

□Induced ovulation treatment

□Clomiphene citrate ( France to Portland , snow Lanfen )

□Letrozole

□Gonadotropin ( including rFSH，HMG）

□Others

□Intrauterine insemination（IUI）

□Traditional Chinese medical science

□Others（please specify）：________________

**Gynecological history**

1. Have you ever received gynecologic operation in the past？□No □Yes

- Ovarian Cyst excision
- Unilateral oophorectomy
- Ovarian drilling technique under laparoscopy（LOD）
- Hysteromyomectomy
- Endometriosis -related surgery
- Infertility-targeted hysteroscopy laparoscopy combined exploratory operation
- Operation for treatment of hydrosalpinx
- Ovarian tumor surgery
- Others

1. GPAL
2. Is your medical history of recurrent spontaneous abortion (Including biochemical pregnancy miscarriage)≥3 times in the past? □Yes □No

**Physical examination & measurement**

Date of examination：//（Y/M/D日）

1. Height cm

2. Weight kg

3. Blood Pressure：/mmHg （Systolic/diastolic）

4. Gynecological examination：□Normal □Abnormal（Please specify：______________________）

**Transvaginal ultrasound B results**

1. Date of examination：//（Y/M/D日）

Menstrual Cycle：Which day

1. Size of the uterus：cm ×cm，

Hsteromyoma：□ No □Yes

□Intramural

□Submucosal

□Subserosal

The number of fibroids：□Single □Multiple

Average diameter of the largest myoma： cm

For other uterine abnormalities, please describe：______________________

Endometrial thickness：cm

Size of right ovary：cm ×cm，oophoritic cyst：

Size of left ovary：cm ×cm，oophoritic cyst：

**Security primary screening test results (valid within the past year):**

| **Test Items** | **Date of Examination** | **Results（Normal√；abnormal × add the details）** |
| --- | --- | --- |
| Blood routine examination |  |  |
| Liver function |  |  |
| Renal function |  |  |
| Coagulation function |  |  |
| Infectious disease screening（HBV, HCV, HIV, syphilis） |  |  |
| Routine urine test |  |  |
| TCT/LCT |  |  |
| Electrocardiogram ECG |  |  |
| DR or |  |  |

**Into-group conditions（****Answer requiring to be "YES"）**

1. The patient's age at the time of informed consent≥20y and ≤40y？□Yes □ No
2. Is the patient have d3 frozen embryos？□Yes □ No

**Exclusion criteria（Answer requiring to be "No"）**

1. Whether or not the patient is diagnosed with uterine abnormalities（Including uterine malformations, adenomyosis, submucous myoma , uterine adhesions）？□No □Yes
2. Whether or not the patient has the medical history of three or more than three times of recurrent spontaneous abortions (Including biochemical pregnancy miscarriage)? □No □Yes
3. Whether or not the patient has the medical history of three or more than three times of embryo transfer failures (Including biochemical pregnancy miscarriage)? □No □Yes
4. Whether or not the patient is taking or receiving drugs or treatments that may affect the reproductive and metabolic function？□No □Yes
5. Based on the above history review and preoperative examination, Whether or not the assisted reproductive technology and pregnancy contraindications exist? □No □Yes

Research Program：A comparison of live birth rates between sustained release vaginal progesterone gel and intramuscular injection of progesterone in hormone replacement frozen-thawed embryo transfer cycles:

**Inspection Visit Form for** **Endometrium Secretory Phase Transformation Date (page 6)**

**Menstrual type before the preparation of hormone replacement endometrial cycles:**

□Spontaneous menstruation □Progesterone withdrawal □ OCP withdrawal

**Estradiol valerate treatment**

Number of days of estrogenic hormone therapy：__ __days

**Endometrial transformation date B-scan results：**

The total number of follicles：14 - 18 mm ( >=14mm且<18mm) piece; >=18 mm piece

Endometrial thickness：mm，typing _____.

**Hormone level of endometrial transformation date：**

E2: ______pg/ml ; LH: ______IU/L; P ______ng/dl

**Endometrial** **transformation**

Date of transformation：__ ____ __/__ __/__ __ （Y/M/D）

**Random front** **scaling conditions（If any one answer is "yes "，the patient should withdrew from the study）**

Endometrial thickness＜7mm？□Yes □ No

**Randomized grouping**

1. Whether or not the patient complies with the random grouping conditions？□ Yes □ No

2. Whether or not the patient agrees to be randomly grouped？□ Yes □ No

3.Date of Randomization：__ ____ __/__ __/__ __（Y/M/D）

4. The patient will be randomly assigned to：

□Group A（sustained release vaginal progesterone gel group）□Group B（Intramuscular progesterone group）

Research Program：A comparison of live birth rates between sustained release vaginal progesterone gel and intramuscular injection of progesterone in hormone replacement frozen-thawed embryo transfer cycles:

**Inspection Visit Form for Embryo Transfer Date** **(page 7)**

**Frozen-thawed** **embryo transfer**

1. Endometrial thickness before transfer：mm；

2. The number of embryos transfer：______

3. The number of remaining frozen-thawed embryos：______

4. Day-old of remaining frozen-thawed embryos：

□D3 □D5

5. Reasons for not-performed embryo transfer：

□Thaw failure of embryos，no available embryo transfer

□Uterine factor

□Others

Research Program：A comparison of live birth rates between sustained release vaginal progesterone gel and intramuscular injection of progesterone in hormone replacement frozen-thawed embryo transfer cycles:

**Inspection Visit Form for Determination of Biochemical Pregnancy (page 8)**

1. Pregnancy test__ days after embryo transfer
2. Blood HCG test value：______IU/L；
3. Whether or not the patient has obtained biochemical pregnancy？□ Yes □ No

Research Program：A comparison of live birth rates between sustained release vaginal progesterone gel and intramuscular injection of progesterone in hormone replacement frozen-thawed embryo transfer cycles:

**Inspection Visit Form for the Date of Clinical Pregnancy Assessment**

**(Page 9)**

1. This B –scan shall be conducted within ___days after the embryo transfer.
2. Whether or not the patient has obtained the clinical pregnancy?

□Yes

The number of intrauterine gestational sac：

The number of embryos with fetal heart beat：

□If no，the results shall be：

□Biochemical pregnancy miscarriage

□Right fallopian tube pregnancy

□Left fallopian tube pregnancy

□CHM

□PHM

□Heterotopic pregnancy

3. EDC of the patient：__ ____ __/__ __/__ __ （Y/M/D）

Research Program：A comparison of live birth rates between sustained release vaginal progesterone gel and intramuscular injection of progesterone in hormone replacement frozen-thawed embryo transfer cycles:

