# 4 Flow chart and visit

## 4.1 Flow chart

Informed consent and screening (menstruation on day 1~3):

- Medical history review
- ultrasound and physical examination

Screening failed

Hormone replacement protocol:

- Estradiol valerate 4 mg/d was administrated on day 3 of menstruation for 10 days;
- 10 days after administration, B-mode ultrasound examination was conducted. If endometrial thickness <7mm, increasing the dose of estradiol valerate to 6-8mg/d;
- If endometrial thickness was ≥7mm, progesterone would be administrated on day 0 to promote endometrium to secretory phase.

Endometrial secretory transformation on day 0

Excluded before random allocation:

Endometrial thickness <7mm

Random allocation

Group A

- Sustained release vaginal progesterone gel 90mg/d
- Dydrogesterone 20mg/d
- Estradiol valerate 4-8mg/d
- Day3 FET

Group B

- Intramuscular progesterone 40mg/d
- Dydrogesterone 20mg/d
- Estradiol valerate 4-8mg/d
- Day3 FET

Determination of pregnancy:

14 days after transfer, blood β-hCG was determined to check whether biochemical pregnancy achieved.

Pregnancy

No pregnancy

- Sustained release vaginal progesterone gel or intramuscular progesterone, dydrogesterone and estradiol valerate were withdrawn.
- Sustained release vaginal progesterone gel or intramuscular progesterone, dydrogesterone and estradiol valerate were administrated continually at the same dose.
- 5 weeks after transfer, vaginal B-mode ultrasound examination was conducted. If gestational sac and fetal heart were observed, it is defined as clinical pregnancy.
- Sustained release vaginal progesterone gel or intramuscular progesterone, dydrogesterone and estradiol valerate were withdrawn.
- 6 weeks after transfer, oral estradiol valerate was withdrawn.
- 8 weeks after transfer, sustained release vaginal progesterone gel or intramuscular progesterone was withdrawn.
- 10 weeks after transfer, dydrogesterone was withdrawn.
- Letter or telephone follow-up was performed to investigate delivery and birth outcomes.

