## 4.6 Visit on the day of evaluation of clinical pregnancy

5 weeks after transfer, vaginal B-mode ultrasound examination was conducted in blood β-hCG positive patients. If gestational sac and fetal heart were observed, it is defined as clinical pregnancy. Patients were asked whether any adverse events had occurred, if any, adverse event reporting form should be completed.

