# 9 Outcome measures

The primary outcome measure was live birth rate and the secondary outcome measures were included clinical pregnancy, miscarriage, ectopic pregnancy and implantation rates.

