# 11Data statistics

## 11.1 Estimation of sample size

Yanushpolsky, et al reported in a RCT study that ongoing pregnancy or live birth rates in sustained release vaginal progesterone gel and intramuscular progesterone groups were 45.2% and 42.2%, respectively, in FET cycles ^[3]^. Two domestic studies were reported respectively that clinical pregnancy rate in 155 patients who received intramuscular progesterone in hormone replacement FET cycles to promote endometrium to secretory phase was 34.8% and in 315 patients was 23.5% ^[8-9]^. Assuming that live birth rate in sustained release vaginal progesterone gel group in hormone replacement FET cycles was 10% higher than that in intramuscular progesterone group (40% in sustained release vaginal progesterone gel group and 30% in intramuscular progesterone group), 675 cycles were required to reach 90% statistical power for each group. Considering about 10% of dropout rate, 750 cycles were required for each group and a total of 1500 cycles for 2 groups.

Calculation of sample size

Significance level α: 0.01

1-β: 0.90

Live birth rate in group A: 0.40

Live birth rates in group B: 0.30

Ratio: 1:1

The minimum sample size: 675 cycles for each groups and a total of 1350 cycles for 2 groups.

Considering about 10% of dropout rate, 750 cycles were required for each group and a total of 1500 cycles for 2 groups.

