## 11.2 Statistical methods

Differences in live birth rates between the two groups were discussed using intentional analysis. Data were compared using statistical software SPSS 19.0. Results were expressed as mean ± standard deviation (X ± SD) or percentage (%).Count data was analyzed using chi-square test and measurement data using T-test.

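### CRF page 9 codes heterotopic pregnancy as no clinical pregnancy and has no box for an ectopic pregnancy outside the tubes, so three secondary outcomes can be miscoded

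*Combined protocol and SAP*

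**What the plan says.** **The outcomes.** Section 9 names the secondary outcomes as "clinical pregnancy, miscarriage, ectopic pregnancy and implantation rates"; section 3 gives the same list. Neither section defines ectopic pregnancy or implantation rate, or says whether a heterotopic case counts as ectopic.

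**The definition of clinical pregnancy.** Section 4.6 states: "If gestational sac and fetal heart were observed, it is defined as clinical pregnancy". The flow chart in 4.1 agrees. Section 5.5 asks for a gestational sac only. None of the three says that the sac must be intrauterine.

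**The form.** CRF page 9 asks whether clinical pregnancy was achieved. Under yes, it collects the number of intrauterine sacs and the number of embryos with a heartbeat. Under no, it offers six results: biochemical loss, right tubal, left tubal, two boxes abbreviated CHM and PHM, and "Heterotopic pregnancy". The page has no free-text line and no box for other results. CRF pages 7 and 10 do have such options.

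**The primary outcome.** The number of live births is recorded on a separate delivery form, CRF page 10, at the follow-up described in 4.7.

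**The concern.** A heterotopic pregnancy is an intrauterine and an extrauterine pregnancy together. If the intrauterine sac and heartbeat are seen at the week-5 scan, the woman is clinically pregnant under 4.1, 4.6 and 5.5, but her only box on the form lies under no. Because the sac and heartbeat fields belong to the other answer, her intrauterine sac may never reach the implantation rate.

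The second gap concerns ectopic pregnancy. A pregnancy outside both the uterus and the tubes, or one whose location cannot be established, has no proper box. The plan names no other source for the ectopic rate. Such a case could be left out or placed in a box that does not describe it.

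At stake is the accuracy of three secondary outcomes: clinical pregnancy, implantation and ectopic pregnancy. Section 5.4 allows transfer of two embryos, and two to three in some women, and the form itself foresees heterotopic cases, so the situation is not far-fetched in this trial.

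**Working it through.** **1. The denominator.** The plan gives no figure for this issue, so the only figure to reproduce is the arm size. Inputs from 11.1: "Significance level α: 0.01", power 0.90, "Live birth rate in group A: 0.40", "Live birth rates in group B: 0.30", ratio 1:1. Sidedness is not stated. I took two-sided, which fits 11.2 ("Count data was analyzed using chi-square test").

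n = [z(0.995)·√(2·p̄·(1−p̄)) + z(0.90)·√(p₁(1−p₁) + p₂(1−p₂))]² / (p₁−p₂)², with p̄ = 0.35

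= [2.576·√0.455 + 1.282·√0.45]² / 0.10² = (1.737 + 0.860)² / 0.01 = 674.5, rounded up to 675.

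Allowing for dropout: 675 / (1 − 0.10) = 750 per arm. Both figures agree with the plan. They rest on live birth and do not depend on page 9.

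**2. The texts side by side.**

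| Finding at the week-5 scan | 4.1 and 4.6 (sac and heartbeat) | 5.5 (sac) | CRF page 9 |
|---|---|---|---|
| Heterotopic, intrauterine sac with heartbeat | Clinical pregnancy | Clinical pregnancy | No; counts not prompted |
| Heterotopic, intrauterine sac, no heartbeat seen | Not met | Clinical pregnancy | No; counts not prompted |
| Tubal sac only | Met on a literal reading if there is a heartbeat | Met on a literal reading | No; own box by side |
| Ectopic sac at another site | Met on a literal reading if there is a heartbeat | Met on a literal reading | No matching box |
| Pregnancy of unknown location (no sac seen) | Not met | Not met | No matching box |

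The first row is a direct contradiction. The second is one between 5.5 and the form, and it also shows the difference between 4.6 and 5.5. The last two rows are the gap in the ectopic outcome.

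**3. Size per woman.** One miscoded woman shifts her arm's clinical pregnancy rate, and one missed case its ectopic rate, by 1/750 = 0.13 percentage points. The documents give no incidence, so the counts below are assumptions:

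| Assumed cases per arm | Shift in that arm's rate |
|---|---|
| 1 | 1/750 = 0.13 points |
| 2 | 2/750 = 0.27 points |
| 5 | 5/750 = 0.67 points |
| 10 | 10/750 = 1.33 points |

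These are shifts within one arm. If both arms lose the same number, the difference between arms does not move.

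**4. Implantation.** The plan does not define the denominator. If it is embryos transferred, and one to three are transferred per woman (an assumption bounded by the upper limits in 5.4), an arm has 750 to 2250 embryos. One lost sac then shifts the rate by 1/750 = 0.13 to 1/2250 = 0.04 points.

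**The case against.** **Heterotopic cases stay identifiable.** They have their own box, so an analyst can count each as ectopic and, where the definition is met, as a clinical pregnancy. Page 9 carries no explicit skip instruction, so a careful investigator could fill in the counts as well. This stands in part. Recovery is possible, but the plan states no such rule, and the form as printed gives the wrong answer to its own question.

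**Other records may hold the missing ectopic cases.** Section 12.1 lists ectopic pregnancy as a risk, 12.2 makes hospitalization a serious adverse event, and 12.3 asks for a diagnosis. A non-tubal case may therefore be recorded there. The plan does not link those forms to the ectopic rate, so the gap in the outcome remains.

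**The form shows that intrauterine is meant.** Its yes branch counts intrauterine sacs and its no branch holds the tubal cases. This is a fair reading, and it makes the literal inclusion of tubal sacs a matter of wording only.

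**Translation and layout.** The CRF is a translation and its layout has been flattened. If the heterotopic box was meant for ectopic pregnancy at another site, true heterotopic cases have no box. If the word is meant literally, other sites have none. Either way one group is without a correct place, but which one must be checked.

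**Stronger readings that the documents do not support.**
- A reader might infer that these women are lost as live births. Section 4.7 does not limit delivery follow-up to women marked yes, page 9 asks for the expected delivery date as a separate item, and page 10 records the birth.
- A reader might infer that the ectopic rate is off by a large share. The documents give no number of ectopic pregnancies and none of non-tubal cases, so that share cannot be computed. Heterotopic cases have a box and are not the missing ones.
- A reader might infer that the form and 4.6 lead to different treatment. The flow chart contains "Sustained release vaginal progesterone gel or intramuscular progesterone, dydrogesterone and estradiol valerate were withdrawn" twice, but its arrows are not available. Section 5.5 ties withdrawal of all support to a negative hCG, and neither 4.6 nor page 9 gives a treatment instruction. All that follows is that the passages must be reconciled where they classify the same woman differently.

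**Conclusion.** The defect holds as one of data collection for secondary outcomes. As printed, page 9 contradicts the definition of clinical pregnancy for a heterotopic case with a living intrauterine embryo, may lose her sac from the implantation rate, and leaves ectopic pregnancies at other or unknown sites without a box. Nothing elsewhere in the documents corrects this.

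It is small: about 0.13 percentage points per affected woman in an arm of 750, with few women likely. That expectation is a judgement, since the documents give no incidence. Both arms use the same form, and no mechanism for a difference between arms is shown. The primary outcome and the sample size are untouched. The conclusion assumes that the nesting of the form and the word heterotopic are faithful to the original-language CRF.

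**What to change.** First check the layout and the wording of the box against the original-language CRF. Then, on page 9, for every hCG-positive woman scanned, record:

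- (a) the number of intrauterine sacs and the number with a heartbeat;
- (b) extrauterine pregnancy, yes or no, with site: left tube, right tube, other, unknown location.

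Derive clinical pregnancy from (a) and ectopic pregnancy from (b), so that a heterotopic case counts in both. Take the sac count for implantation from (a). Add the word intrauterine to the definitions in 4.1, 4.6 and 5.5, and reconcile those sections on whether a heartbeat is required.

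The cost is the layout of one CRF page and a short edit in three sections, with no extra visit or procedure. If data have already been collected, the same rule can be applied by reviewing the scan records of the hCG-positive women marked no.
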